### Follow-up

#### Assessments

The duration of the first stage of labor is determined in minutes and written in the questionnaire. To assess the pain score, pain measurement using a VAS (visual analogue scale) ruler will be used at 4- and 10-cm dilations. Furthermore, the midwifery and demographic characteristics questionnaires are completed after finishing the birth.

#### Administration of intervention

Selection of acupoints is based on ear and body microsystems and meridians. Some treatment plans include a combination of some acupoints for every problem. These selections of points were originally derived from treatment plans developed in China, but modified by auriculotherapy discoveries in Europe and the United States. Theoretically, every acupoint can exert some identified effect for the selected condition [27–30]. For the present research, a set of primary and master acupoints was selected. Using combination sets of points is proposed to be more effective than single points. As there is scant evidence on the efficacy of applying multiple acupoints, we aim to investigate the efficacy of multiple acupoints on labor pain and duration.

In the body acupressure group, pressure is applied to the GB30, GB21, BL32, LI4, and SP6 points [13, 29] (Fig. 2) by a researcher who has been well trained for this purpose. The GB21 point has an action of release and descent, which is purported to facilitate fetal descent in the active phase and second stage of labor [31]. Stimulating the LI4 point is effective for reduction of labor pain and promoting stronger and/or more coordinated contractions [9, 32–34]. Stimulating BL32 is effective for the reduction of labor pain and induction of labor [35, 36]. One of the most important and frequently used points for obstetric and gynecologic concerns is SP6. Indications of this point include labor augmentation, for irregular contractions to encourage efficient labor and reducing a persistent cervical lip [37–39], reduction of labor pain [34, 38–41], and reduction of the length of labor [34, 38]. To perform the acupressure on the specified points on the body, each point will be pressed by the thumb for 2 min, so that one-third of the nail bed becomes white. Pressure to these points would be applied at 4, 6, and 8-cm dilations.

**Fig. 2 Fig2:**
[figure not shown]
Body acupoints

In the auricular acupressure group, pressure will be applied to the master auricular points on the external ear (point zero, Shen Men point, and thalamic point) and primary auricular points (uterus points 1 and 2, external genitalia point, oxytocin and/or prostaglandin points) [27] by a well-trained researcher. Ear acupoints are shown in Fig. 3. The master points are so identified because they are typically active in most patients and they are useful for the treatment of a variety of health disorders. Point zero brings the whole body toward homeostasis, producing a balance of energy, a balance of hormones, and a balance of brain activity and is frequently combined with the Shen Men point for treatment of most health disorders. The purpose of Shen Men is to tranquilize the mind and to facilitate a state of harmony, serenity, and a deeper connection to one’s essential spirit. This master point alleviates stress, pain, tension, anxiety, depression, insomnia, restlessness, and excessive sensitivity. The thalamic point affects the relay of sensory information to the cerebral cortex and modulates hypothalamic regulation of autonomic nerves and endocrine glands. It is also used for alleviating most pain disorders, both acute and chronic. Primary auricular points are the most effective set of auricular points for the treatment of a health disorder in a particular body organ or for a physiological dysfunction [27]. The given pressure will be applied using an adhesive containing auriculotherapy-specific Vakharia seeds. Furthermore, auricular stimulation at the specified points will be performed every 30 min. It should be noted that the comparator group will receive routine care (Fig. 4).

**Fig. 3 Fig3:**
[figure not shown]
Ear acupoints

**Fig. 4 Fig4:**
[figure not shown]
SPIRIT Schedule of enrolment, interventions, and assessments

### Intervention fidelity

One of the researchers (MG) responsible for intervention is trained to perform auriculotherapy. Training and monitoring of her performance on implementing the intervention will be carried out by MV, who is an expert in this field.

### Primary outcome measurements

#### Pain score in the first stage of labor

In the present study, the pain score (pain intensity) at 4- and 10-cm dilations is measured in all three groups using a VAS and then compared.

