Auriculotherapy (AT; also known as auricular therapy) is a branch of acupressure spreading throughout the world. AT is based on a long-standing tradition and was modified and updated by [name]. Also, the World Health Organization considers AT a form of microacupuncture that can affect the whole body [16]. AT comprises several types of therapy, including auricular acupuncture, electro-stimulation, and acupressure. Various studies have reported promising results when using AT for the control of pain caused by backache, [17] pelvic fractures, [18] dysmenorrhea, [19–21] and polycystic ovarian syndrome [22]. However, only a limited number of studies have been done on the effect of auriculotherapy on labor pain, and these have yielded inconsistent results. Accordingly, in Rastegarzadeh et al.’s work, auriculotherapy led to a significant reduction in labor pain among nulliparous women [23], whereas a study by Maftoni and Shimo indicated that use of auriculotherapy caused no significant reduction in the studied women’s labor pain [24].

As can be inferred from investigations, most of the studies on body acupressure have more frequently applied pressure on one or two points; only a few studies have focused on a combination of points affecting the pain and progress of labor. Furthermore, some studies have been conducted on the effect of auricular acupressure on the reduction of different pain throughout the body, the results of which have confirmed the effectiveness of this technique. However, only a few studies have addressed the effect of auricular acupressure on labor pain, yielding inconsistent results [3, 4]. Given the small number of studies on the effect of body acupressure at multiple points and auricular acupressure on the pain and duration of labor, we designed the present study. In this clinical trial, the primary objective is to compare the effects of auricular acupressure, body acupressure, and routine treatment on the pain score at the time of 4-cm and 10-cm cervical dilations. The secondary objective is to investigate the effects of the described interventions on the duration of the first stage of labor, which is defined as the time interval between the 4 cm and 10 cm cervical dilations. This is a single-center, parallel, double blinded randomized controlled trial to investigate the superiority of auricular acupressure and body acupressure compared with routine care during the first stage of labor. The allocation ratio for the groups is 1:1:1.

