#### Data collection and storage‌

Based on the predetermined allocation sequence, the studied women are divided into three groups, auricular acupressure, body acupressure, and routine care groups. The pain score for all participants will be measured at the peak uterine contraction at 4-cm cervical dilation and then recorded in the questionnaire. Subsequently, at 10-cm dilation, the pain score of all participants in the three groups will be re-measured and recorded. Furthermore, in order to investigate the duration of the active phase of labor in these groups, the onset and termination times of the active phase of the first stage of labor will be recorded in the questionnaire. The difference of these two recorded times indicates the duration of this stage. The remaining parts of the questionnaire are completed after the birth. Ethics committee will monitor the whole procedure including data gathering.

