### Data analysis

Once collected, the data are imported into SPSS-16 software. Firstly, normality of the data distribution will be investigated (via three methods, including Kolmogorov–Smirnov, histogram, and dispersion and central indices) and if the distribution of variables is not normal, then we will use an appropriate transformation. To compare the labor duration and pain score among the research groups, one way ANOVA test will be used, which will be followed, in case of significance, by Scheffe post hoc test. If there are potential confounding variables, a multiple linear regression test will be used. We will check for the assumptions and concerns of the regression model. Furthermore, Chi-squared test will be used to compare the categorized demographic variables in the studied groups. In order to compare the quantitative variables, in case of normal and abnormal distribution of the variables, ANOVA and Kruskal–Wallis tests will be used, respectively. The post hoc of these tests will be reported if needed. The study will be analyzed using an intention-to-treat (ITT) approach and using a multiple imputation strategy to account for missing outcomes in ITT. Also, apropos of the significance level, 0.05 is considered significant.

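### The 4-cm pain score, most likely a baseline, is listed as a primary outcome and is not a prespecified covariate for the 10-cm score; the 10-cm comparison stays valid but loses precision

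*Protocol article*

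**What the plan says.** All references are to the protocol article.

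- **Objective (Background).** The main aim of the trial reads: "compare the effects of auricular acupressure, body acupressure, and routine treatment on the pain score at the time of 4-cm and 10-cm cervical dilations".
- **Primary outcome (Pain score in the first stage of labor).** "the pain score (pain intensity) at 4- and 10-cm dilations is measured in all three groups using a VAS and then compared". The two times are not ranked and no alpha is divided between them.
- **Measurement (Data collection and storage).** "The pain score for all participants will be measured at the peak uterine contraction at 4-cm cervical dilation and then recorded in the questionnaire"; then, "at 10-cm dilation, the pain score of all participants in the three groups will be re-measured and recorded".
- **Entry (Inclusion criteria).** Women are admitted at 3–4 cm dilation.
- **Treatment (Administration of intervention).** For body acupressure, "Pressure to these points would be applied at 4, 6, and 8-cm dilations". For the ear points, "auricular stimulation at the specified points will be performed every 30 min"; the text gives no starting point.
- **Analysis (Data analysis).** "To compare the labor duration and pain score among the research groups, one way ANOVA test will be used", with Scheffé comparisons if it is significant, at the 0.05 level. Multiple linear regression is to be used if potential confounders exist. The 4-cm score is not named there.

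**The concern.** The first pain measurement and the first body acupressure session fall at the same dilation. If the VAS comes first, the 4-cm score is a pre-treatment value. In a randomized trial any difference between arms on it is then chance, so it should not stand beside the 10-cm score as a place to look for an effect.

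Two things are at stake. First, a chance difference at 4 cm could be reported as a primary result. Second, a baseline measurement of the same quantity on the same scale is normally the most useful covariate available. The plan collects it but does not commit to using it, in a trial whose power is already tight.

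**Working it through.** **Inputs.** Sample size estimation gives a 1-point important difference, SD 1.4, alpha 0.05, power 0.80, 10% dropout and 30 per group. With 10% loss, 30 × 0.9 = 27 evaluable per arm. The correlation r between the 4-cm and 10-cm scores is not in the documents; I take 0.2 to 0.7 as an assumed range. The article does not say which time point the SD describes; I apply it to the 10-cm score.

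**The plan's own figure.** For a three-group ANOVA with one arm 1 point from the other two, f = 0.471/1.4 = 0.337, which needs 30 per group before dropout and 34 after. A two-sided pairwise t test needs 32, or 36 after dropout. A one-sided test needs 25, or 28 after dropout. So 30 matches the ANOVA before dropout, or comes within 2 of the one-sided figure after it. Under a two-sided or ANOVA test there is no power to spare.

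**Two primary tests.** Suppose each time point is tested by ANOVA at 0.05 and nothing has any effect. If the scores are independent, the chance of at least one significant result is 1 − 0.95² = 0.0975. Simulation of correlated scores (27 per arm, 100,000 replicates) gives:

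| r | At least one significant |
|---|---|
| 0 | 0.097 |
| 0.3 | 0.095 |
| 0.5 | 0.093 |
| 0.7 | 0.086 |

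The 10-cm test on its own stays at 0.05.

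**Precision.** Adjusting for a baseline with correlation r leaves a residual SD of 1.4 × √(1 − r²). The SE of a difference between two arms is that SD × √(2/27), and the noncentrality is 1/SE. Error degrees of freedom are 81 − 3 = 78 unadjusted and 77 adjusted.

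Unadjusted: SE = 1.4 × 0.272 = 0.381, noncentrality 2.62, critical t 1.99, power 0.736. The Scheffé critical value is √(2 × F(0.95; 2, 78)) = 2.50, which gives power 0.55.

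| r | Residual SD | SE | Power, pairwise t | Power, Scheffé contrast |
|---|---|---|---|---|
| unadjusted | 1.400 | 0.381 | 0.74 | 0.55 |
| 0.2 | 1.372 | 0.373 | 0.75 | 0.57 |
| 0.3 | 1.336 | 0.363 | 0.78 | 0.60 |
| 0.4 | 1.283 | 0.349 | 0.81 | 0.64 |
| 0.5 | 1.212 | 0.330 | 0.85 | 0.70 |
| 0.6 | 1.120 | 0.305 | 0.90 | 0.78 |
| 0.7 | 1.000 | 0.272 | 0.95 | 0.88 |

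The gain in t power is 2 to 4 points at r = 0.2–0.3 and about 11 points at r = 0.5. These figures treat 27 per arm as complete cases; the plan uses multiple imputation, which I have not modelled.

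**The case against.** - **Two tests are not stated.** A reader might infer that the plan tests 4 cm and 10 cm separately at 0.05. The analysis section names one-way ANOVA for the pain score without giving a time point, so an analysis of change or of 10 cm alone is not excluded. This objection stands: separate tests are one reading of an ambiguous text.
- **The false-positive rate is not simply doubled.** If the 4-cm score is a baseline, a difference there is no evidence of efficacy, and the 10-cm test keeps its 5% level. The 9–10% arises only if a 4-cm difference is read as a treatment effect. This also stands, although an objective worded as effects "on the pain score at the time of 4-cm and 10-cm cervical dilations" invites that reading.
- **The measurement order may be specified elsewhere.** A reader might conclude that the trial has no baseline pain score. The text does not support that. The second score is described as a re-measurement, which fits a before-and-after design, and the flow chart and SPIRIT schedule are figures not shown here.
- **Regression is already allowed.** The confounder clause could take in the 4-cm score, and covariate lists are often left to an analysis plan. This stands only in part: the clause depends on what the data show and does not name the score, while the article itself fixes ANOVA as the test.
- **Unadjusted ANOVA is valid.** It is unbiased under randomization, and its standard error already allows for chance imbalance. This stands. The loss is one of precision only.

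**Conclusion.** The concern holds in limited form. Listing the 4-cm score as a primary outcome is a poor choice, because it is most likely a baseline; that is a strong inference from the entry criterion, the treatment schedule and the measurement sequence, not something the text says outright. The 10-cm comparison as planned is not invalid. It gives up precision of unknown size: at 27 per arm, pairwise t power of 0.74 would become anything from 0.75 to 0.95 over assumed correlations of 0.2 to 0.7. Under the planned Scheffé contrasts the corresponding figures are 0.55 and 0.57 to 0.88. The 9–10% false-positive chance is conditional on separate tests at 0.05 and on reading either one as efficacy.

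**What to change.** 1. Name the 10-cm VAS as the single primary outcome, in both the objective and the outcome section.
2. Replace one-way ANOVA for pain with a prespecified linear model for the 10-cm VAS, with arm and 4-cm VAS as terms (ANCOVA), reporting adjusted differences between arms with 95% confidence intervals. Do not make the adjustment depend on observed imbalance.
3. Show the 4-cm score only among the baseline characteristics, without an efficacy test.
4. Confirm in the text that the 4-cm VAS precedes the first session in every arm, including the auricular arm. A score taken after the first session could already carry some treatment effect and would not be a clean covariate.

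The cost is one degree of freedom and a wording change, since the score is already collected. The analysis items can be settled before the group codes are opened. Recruitment began in August 2018 and data collection was expected to finish around December 2019, so for most participants item 4 can only document what was done. If the order turns out to be otherwise, keep the 10-cm score as sole primary outcome and leave the 4-cm score out of the primary model.

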### Additional outcomes

#### Duration of the first stage of labor

The present study is aimed to determine whether auricular acupressure and body acupressure can reduce the duration of the first stage of labor in nulliparous women compared to routine care.

#### Data collection and storage‌

Based on the predetermined allocation sequence, the studied women are divided into three groups, auricular acupressure, body acupressure, and routine care groups. The pain score for all participants will be measured at the peak uterine contraction at 4-cm cervical dilation and then recorded in the questionnaire. Subsequently, at 10-cm dilation, the pain score of all participants in the three groups will be re-measured and recorded. Furthermore, in order to investigate the duration of the active phase of labor in these groups, the onset and termination times of the active phase of the first stage of labor will be recorded in the questionnaire. The difference of these two recorded times indicates the duration of this stage. The remaining parts of the questionnaire are completed after the birth. Ethics committee will monitor the whole procedure including data gathering.

### Data analysis

Once collected, the data are imported into SPSS-16 software. Firstly, normality of the data distribution will be investigated (via three methods, including Kolmogorov–Smirnov, histogram, and dispersion and central indices) and if the distribution of variables is not normal, then we will use an appropriate transformation. To compare the labor duration and pain score among the research groups, one way ANOVA test will be used, which will be followed, in case of significance, by Scheffe post hoc test. If there are potential confounding variables, a multiple linear regression test will be used. We will check for the assumptions and concerns of the regression model. Furthermore, Chi-squared test will be used to compare the categorized demographic variables in the studied groups. In order to compare the quantitative variables, in case of normal and abnormal distribution of the variables, ANOVA and Kruskal–Wallis tests will be used, respectively. The post hoc of these tests will be reported if needed. The study will be analyzed using an intention-to-treat (ITT) approach and using a multiple imputation strategy to account for missing outcomes in ITT. Also, apropos of the significance level, 0.05 is considered significant.

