### Inclusion and exclusion criteria

#### Inclusion criteria

The inclusion criteria in the present study are primigravida women aged 19–35 years at gestational age of 37–42 weeks with a singleton pregnancy, cephalic presentation, no history of chronic diseases such as diabetes, cardiovascular disease, hypertension, hepatic and renal disorders, etc., a lack of pregnancy complications such as preeclampsia, gestational diabetes, bleeding, etc., a height above 150 cm, and admission at the beginning of the active phase (3–4 cm dilation).

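### Recorded labour duration may depend on whether a woman enters at 3 or 4 cm; the main duration analysis should adjust for admission dilation by pre-specification, and the clock start should be stated consistently

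*Protocol article*

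**What the plan says.** All references are to the protocol article.

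- **Entry (Inclusion criteria).** Women are eligible on "admission at the beginning of the active phase (3–4 cm dilation"), so they may enter at either dilation.
- **Definition of duration (Background).** The first stage is the secondary outcome, "which is defined as the time interval between the 4 cm and 10 cm cervical dilations".
- **Recording of duration (Data collection and storage).** Here "the onset and termination times of the active phase of the first stage of labor will be recorded in the questionnaire", and duration is the difference between the two times. The 4 cm anchor is not repeated.
- **Analysis (Data analysis).** "To compare the labor duration and pain score among the research groups, one way ANOVA test will be used", followed by Scheffé comparisons if significant. The next sentence adds: "If there are potential confounding variables, a multiple linear regression test will be used". It names no variable and gives no criterion for deciding that one is a confounder.
- **Role of the outcome (Background).** "The secondary objective is to investigate the effects of the described interventions on the duration of the first stage of labor". The sample size rests on the pain score, not on duration.

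**The concern.** The three statements about time do not fix one clock start for every woman, and each reading leaves a route by which admission dilation can enter the recorded duration.

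- **Clock starts at 4 cm.** A woman admitted at 3 cm can be observed up to 4 cm. A woman already at 4 cm on admission got there at a time nobody recorded. Unless that time is recovered somehow, her clock starts at admission and her interval is cut short.
- **Clock starts at onset of the active phase.** The inclusion criteria place the beginning of that phase at 3–4 cm, so a woman admitted at 3 cm may simply be started earlier.

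If either route operates, part of the spread in duration is explained by a value known before randomisation. The one-way ANOVA leaves that part in the error term. The regression that could remove it depends on a condition that can be judged only once data are in hand. This also leaves open whether the unadjusted or the adjusted result is the main one for duration. What is at stake is the precision of a secondary comparison with 30 women per arm, and a clear statement of which result counts.

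**Working it through.** **The plan's own figure.** None exists for duration. The 30 per group was derived for the pain score and is not affected by this point.

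**Inputs.** From the document: 30 women per arm, three arms, entry at 3 or 4 cm. Not in the document, and assumed here: half the women admitted at each dilation (p = 0.5); a gap g of 30, 60 or 120 min in mean recorded duration between the two entry groups; a residual SD s of 90 or 120 min within entry group.

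**Step 1. Variance explained by admission dilation.**
R² = p(1−p)g² / [p(1−p)g² + s²] = 0.25g² / (0.25g² + s²).
Example, g = 120 and s = 90: 3600 / (3600 + 8100) = 0.308.

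**Step 2. Effect of adjustment on the standard error.** Adjusted SE / unadjusted SE = √(1−R²). For the same example, √0.692 = 0.832, a fall of about 17%.

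**Step 3. Power.** For an effect with 0.80 power unadjusted (two-sided 0.05), adjusted power = Φ[(1.960 + 0.842)/√(1−R²) − 1.960].

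| Gap g (min) | Residual SD s (min) | R² | SE ratio | Power (0.80 unadjusted) |
|---|---|---|---|---|
| 0 | 90 or 120 | 0 | 1.000 | 0.80 |
| 30 | 120 | 0.015 | 0.992 | 0.81 |
| 30 | 90 | 0.027 | 0.986 | 0.81 |
| 60 | 120 | 0.059 | 0.970 | 0.82 |
| 60 | 90 | 0.100 | 0.949 | 0.84 |
| 120 | 120 | 0.200 | 0.894 | 0.88 |
| 120 | 90 | 0.308 | 0.832 | 0.92 |

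**Step 4. Chance imbalance.** The SD of the difference in the proportion admitted at 3 cm between two arms of 30 is √(0.25 × 2/30) = 0.129, or 13 percentage points. A one-SD imbalance moves the difference between two arms by 0.129 × g = 3.9, 7.7 or 15.5 min.

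**Step 5. Is that shift extra error?** The unadjusted SE of a difference between two arms is √[(0.25g² + s²) × 2/30]. It is √(8325 × 2/30) = 23.6 min at g = 30, s = 90, and √(18000 × 2/30) = 34.6 min at g = 120, s = 120. The shift in Step 4 is one component of this SE. For g = 120, s = 90, the residual part is 90 × √(2/30) = 23.2 min, and √(15.5² + 23.2²) = 27.9 min, which equals √(11700 × 2/30). The ANOVA's standard error therefore already contains it.

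**Step 6. Cost.** With 90 women and three arms the error degrees of freedom are 87. One binary term leaves 86.

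**The case against.** The strongest reply is that the Background sets the interval at 4 to 10 cm. First pain scoring and the first body acupressure session are also set at 4 cm. On that definition the time from 3 to 4 cm is outside the outcome, and the mechanical dependence is zero. A reader might infer from the entry range alone that admission dilation drives the recorded duration; the document does not support that. What it does not guarantee is that arrival at 4 cm is observed for every woman, so zero dependence is not assured either.

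The size, and even the direction, of any gap is uncertain. Requiring "admission at the beginning of the active phase" limits how long a woman can have been at 4 cm. A woman admitted at 3 cm is seen to reach 4 cm only when next examined, so her start may also be recorded late. Examination timing is not given. This stands, and it is why the gap above is an assumption only.

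A reader might also infer that the unadjusted ANOVA is biased or invalid, or that the 4 to 15 min shift is error added to it. Neither follows. Under randomisation the test is valid, and Step 5 shows that the shift is already in the standard error.

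Finally, adjustment is foreseen, and the choice of covariates is commonly left to an analysis plan that is not shown. The first part is true. But the article does more than stay silent: it sets an unadjusted test as the comparison and makes adjustment conditional on an undefined trigger. The point concerns that stated rule. It is also true that a 3-versus-4 cm term does not restore an unobserved start time. It removes only the average difference between the entry groups, so the clock start needs its own correction.

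**Conclusion.** The point holds as a low-cost improvement to a secondary analysis. The passages on entry, definition and recording do not settle one clock start, so recorded duration may depend on admission dilation. The planned ANOVA is sound in its error rate and unbiased, but it forgoes any precision that this baseline value could give, and it leaves adjustment to a decision made after the data are seen.

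Under the assumed inputs, R² is about 0.02 to 0.31 and the standard error falls by about 1% to 17%. The upper figure needs the largest gap together with the smaller residual SD; at a 60 min gap the fall is 3% to 5%. If recorded duration does not depend on entry dilation, the gain is nil. The document supplies none of the three inputs, so the benefit cannot be shown from it. The case for the change rests on its negligible cost and on replacing a conditional choice with a fixed one.

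**What to change.** 1. In Data analysis, name as the main analysis of duration a linear model with arm and admission dilation (3 versus 4 cm), reporting adjusted mean differences between arms with 95% confidence intervals. The overall test of arm and the Scheffé follow-up can be carried out within this model. Fit it whether or not the arms look balanced. The unadjusted ANOVA can be reported as supportive.
2. In Data collection and storage, state that the clock starts at 4 cm, in agreement with the Background, and say which time is entered for a woman already at 4 cm on admission.

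The cost is a sentence in each section and one of 87 error degrees of freedom. Admission dilation is already assessed for eligibility and only has to be kept with the analysis data. No extra women, assessments or stratified randomisation are needed.

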### Sample size estimation

To calculate the minimal clinically important difference (MCID) for the duration of the first stage of labor and the pain score, we used previous study data which examined the effect of auricular [24] and body [25] acupressure on labor pain intensity and labor duration. Using the method of Wyrwich et al. [26], MCID score for significant pain reduction during labor was one score based on visual analogue scale. Using the G*Power software 3.1.9.2, α = 0.05, and power = 0.80, considering SD = 1.4 and M0 = 7.2 for the labor pain score and 10% drop out of subjects, the sample size was calculated to be 30 patients for each group.

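### Scheffe after the ANOVA is valid but needlessly conservative for three pairwise questions: about 4 points of power lost per comparison against Tukey, about 12 against F-protected contrasts

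*Protocol article*

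**What the plan says.** The Data analysis section fixes the procedure for labor duration and pain score: "one way ANOVA test will be used, which will be followed, in case of significance, by Scheffe post hoc test". The significance level is 0.05. The section names no contrast beyond comparisons between groups.

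The Background section gives the aim as "to investigate the superiority of auricular acupressure and body acupressure compared with routine care", and its primary objective also compares the two acupressure methods with each other, as the title does. "The allocation ratio for the groups is 1:1:1", so there are three equal arms.

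The Sample size estimation section works with "α = 0.05, and power = 0.80". It says that the "MCID score for significant pain reduction during labor was one score based on visual analogue scale", uses an SD of 1.4 and a reference mean of 7.2 ("considering SD = 1.4 and M0 = 7.2 for the labor pain score"), and ends with "10% drop out of subjects, the sample size was calculated to be 30 patients for each group". It mentions no allowance for post hoc adjustment.

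**The concern.** Scheffe's critical value is set so that every possible linear contrast among the means is protected, including averages of two arms against the third. This trial has three questions, all pairwise: auricular against routine care, body against routine care, and auricular against body. The plan therefore pays for protection that it does not use.

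The preliminary F test also does nothing for Scheffe. A significant Scheffe contrast already implies a significant F, so the two-step rule gives the same answers as Scheffe alone. Yet with exactly three groups, that same F test would by itself justify unadjusted pairwise contrasts at 0.05.

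What is at stake is the chance of attributing a real effect to a named method, and above all of showing that both methods beat routine care.

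**Working it through.** **Inputs from the protocol article.** Alpha 0.05, planned power 0.80, SD 1.4, reference mean 7.2, difference 1 point, 30 per arm, 10% dropout (30 × 0.9 = 27 evaluable), three arms at 1:1:1.

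**Assumption, not in the article.** True means of 7.2 (routine care), 6.2 and 6.2. Other patterns are examined below.

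**The plan's own figure.** The article names neither the test nor its sidedness.
- One-sided two-sample comparison: (1.645 + 0.842)² × 2 × 1.4² / 1² = 24.2, so 25 per arm, and 25/0.9 gives 28.
- Two-sided: 31 by the normal approximation or 32 by the t distribution, giving 35 or 36 after dropout.
- One-way ANOVA with 7.2/6.2/6.2: 30 before dropout, and 30/0.9 gives 34.

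So 30 is close to the one-sided figure with dropout, and equal to the ANOVA figure without it. Neither allows for a post hoc adjustment.

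**Smallest difference that can be declared.** SE = 1.4 × √(2/n), which is 0.381 at n = 27 and 0.361 at n = 30. The Scheffe critical value is √(2 × F(0.95; 2, 3n − 3)). Multiplying critical value by SE:

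| | Scheffe | Tukey | t after significant F |
|---|---|---|---|
| Critical value, n = 27 (78 df) | 2.496 | 2.389 | 1.991 |
| Smallest difference, n = 27 | 0.95 | 0.91 | 0.76 |
| Critical value, n = 30 (87 df) | 2.491 | 2.384 | 1.988 |
| Smallest difference, n = 30 | 0.90 | 0.86 | 0.72 |

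Bonferroni for three comparisons (2.441 at 87 df) also lies below Scheffe.

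**Power under 7.2/6.2/6.2.** Scheffe and Tukey per comparison come from the noncentral t; the F-protected procedure comes from 500,000 simulated trials per scenario.

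| | Scheffe | Tukey | F-protected contrasts |
|---|---|---|---|
| One comparison with routine care, n = 27 | 0.55 | 0.59 | 0.68 |
| One comparison with routine care, n = 30 | 0.61 | 0.65 | 0.73 |
| Both arms better, n = 27 | 0.39 | – | 0.60 |
| Both arms better, n = 30 | 0.45 | – | 0.66 |

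At n = 30 the loss per comparison is 0.733 − 0.610 = 0.123 against F-protected contrasts and 0.650 − 0.610 = 0.040 against Tukey. At n = 27 it is 0.679 − 0.553 = 0.126 and 0.594 − 0.553 = 0.041.

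**Dependence on the means (1-point contrasts, n = 30, Scheffe against F-protected).**
- 7.2/6.7/6.2: 0.669 − 0.610 = 0.059
- 7.2/7.2/6.2: 0.733 − 0.611 = 0.122
- 7.2/6.2/5.2: 0.781 − 0.609 = 0.172

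**Error control.** With all means equal and n = 30, family-wise error is 3.8% for Scheffe, 5.0% for Tukey and 5.0% for F-protected contrasts. Without the F test, unadjusted contrasts would give 12.1%. When two arms are equal and the third differs by 1 point, the equal pair is falsely declared different in 4.9% to 5.0% of trials under the F-protected procedure. This is what closed testing predicts: with three groups, once the global null is false, at most one pairwise null can be true.

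**Significant F with no significant Scheffe pair.** Under 7.2/6.2/6.2: 0.762 − 0.715 = 0.047 at n = 27, and 0.810 − 0.767 = 0.043 at n = 30.

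**The case against.** The strongest reply is that nothing here is wrong: ANOVA followed by Scheffe is prespecified, standard and inflates no error rate. That stands, and it limits the point to efficiency.

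Second, the 12 points are measured against the most powerful valid alternative under assumed means. Against Tukey, the usual all-pairs method, the loss is about 4 points. A reader might infer a fixed 12-point loss; the article gives no pattern of means to support that.

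Third, a reader might infer that the trial would often reject the overall hypothesis and be unable to name a method. In the main case this happens in only 4% to 5% of trials. The larger loss is in showing that both methods work.

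Fourth, Scheffe does buy something. Its actual family-wise error is below 5%, and its simultaneous intervals agree with its tests. F-protected contrasts lack such intervals. With ordinary 95% intervals, at least one would exclude zero despite a non-significant F in 0.900 − 0.810 = 9% of main-case trials at 30 per arm, in 0.868 − 0.762 = 11% at 27, and in 0.121 − 0.050 = 7% at 30 per arm when all means are equal. So it would be wrong to say that a change costs nothing.

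Fifth, the threshold near a full point is largely a matter of sample size: at 27 per arm, Tukey's is 0.91.

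What survives is that any pair Scheffe declares different would also be declared by Tukey and by the F-protected contrasts, both of which hold 5%. For the planned comparisons, Scheffe has no advantage in power.

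**Conclusion.** The point holds as a cheap gain in efficiency, not as the correction of an error. With SD 1.4, a 1-point effect in both arms and 27 to 30 women per arm, Scheffe has 55% to 61% power per comparison with routine care. That is about 4 points below Tukey and about 12 below F-protected contrasts. Against the latter, the loss for 1-point contrasts runs from about 6 to 17 points across the patterns of means examined at 30 per arm. The figures rest on those assumed patterns, normal data and a common SD.

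Two stronger readings are not supported. Scheffe does not make the analysis invalid. Nor would replacing it deliver the planned 80% per comparison: even F-protected contrasts reach only 68% to 73%, so the remaining shortfall lies in the sample size.

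**What to change.** Before the group codes are opened, replace the Scheffe step in the Data analysis section with one of these:

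- **Closed procedure:** omnibus F at 0.05; if significant, the three pairwise contrasts from the same model, each at 0.05. State that this is valid because there are exactly three groups.
- **Tukey for all pairs,** if simultaneous confidence intervals consistent with the tests are wanted.

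Dunnett would cover only the two comparisons with routine care and would leave out auricular against body, which the title and the primary objective include.

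The cost is one sentence and no new data. The closed procedure has no matching simultaneous intervals and needs a pooled omnibus F under the planned multiple imputation. Either option gives up Scheffe's cover for complex contrasts, which the plan does not use. Timing matters: the Trial status section expected data collection to end in December 2019, so the change should be dated and made while the analyst is still blind.
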